### MNC infusion

All infusions will be administered in the NICU. Infusion and subject identities will be double-checked by research nursing and physician staff. Infusions will be monitored by research and clinical staff. ACBMNCs or placebo are administered intravenously *via* a central catheter or a peripheral catheter if a central catheter is not available. ACBMNC infusion should be performed within 4 h of patients arriving in hospital. The maximum volume will be less than 20 ml/kg. An infusion pump is used to control the infusion rate at less than 10 ml/kg/h. A blood filter will be used to filter the cell settings or blood clots before infusion. Prior to infusion, the intravascular (IV) line is prestored with 2 ml MNCs. We will infuse the MNCs by positioning the syringe and IV line vertically (29). During infusion, the nurses will shake the cells gently every half an hour. After infusion, 2-ml normal saline will be used to flush the intravascular catheter (Figure 2F).

### Safety monitoring and co-intervention

Assessment of safety is conducted before, during, and 12 and 24 h after infusion. The heart rate, systolic, diastolic, and mean arterial blood pressure, and arterial blood oxygen saturation level are monitored continually and documented; these are also monitored during the period of hospitalization and return visits. The levels of arterial blood gas and blood glucose in peripheral blood are monitored and kept stable during the whole treatment period. Infusion reactions (fever, hemolysis, hyperbilirubinemia, and urine color changes) and signs of circulatory overload (tachycardia, dyspnea, edema, and hepatomegaly) are observed and checked during infusion and 48 h after infusion.

The trial will be strictly monitored by the members of a safety monitoring board comprising an ethics committee member, project principal, good clinical practice member, and statisticians, and they will be notified of any severe adverse events (including death, LOS, NEC, severe IVH, and cystic periventricular leukomalacia). Other adverse or unexpected events will be reviewed immediately after they are discovered. After each interim analysis (every 3 months), the data safety monitoring board will make a decision on whether to stop or continue the trial based on safety monitoring and sequential analysis of the primary outcome.

All patients in the study will be given intensive care therapy in accordance with uniform guidelines, which include positive-pressure mechanical ventilation, oxygen therapy, and exogenous pulmonary surfactant (PS) (Curosurf, Chiesi, Parma, Italy) replacement. Oxygen saturation targets (90%–95%), ventilatory support, postnatal steroids, and transfusion guidelines are uniformly given and applied to all enrolled patients. Inhaled nitric oxide is given if a patient with severe hypoxemic respiratory failure presents with severe persistent pulmonary hypertension of newborn (PPHN) confirmed by cardiac ultrasound with an estimated peak systolic pulmonary artery pressure that is higher than 35 mm Hg or more than two-thirds of the systemic systolic pressure. Ibuprofen is given to neonates who have significant patent ductus arteriosus (PDA) (28). Postnatal systemic dexamethasone is reserved only for infants who have severe underlying lung disease and intractable respiratory failure. In such infants, a short course of dexamethasone (three to five doses of 0.25 mg/kg every 12 h) is given at the discretion of the attending physician. Chest radiography is performed after the umbilical venous catheter is placed. Arterial blood gas is monitored at least every 24 h until weaning from ventilation. All clinical diagnoses are defined according to a standard reference (29).

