## Methods

### Study design and settings

This study protocol describes a randomized, placebo-controlled, double-blinded, and multicenter trial to be conducted at seven medical centers (Guangdong Women and Children Hospital, Dongguan Maternal and Child Health Hospital, Zhongshan Boai Hospital, Shunde Hospital-Southern Medical University, Dongguan Hospital-Southern Medical University, Nanfang Hospital-Southern Medical University, and Affiliated Maternal and Child Hospital of Foshan-Southern Medical University) in tertiary hospitals. The participating NICUs are selected by an expert committee based on the distance to the Guangdong Cord Blood Bank (GDCBB) and the level of intensive care that these NICUs could provide. The Guangdong Cord Blood Bank is a public provincial blood bank affiliated with the Guangdong Women and Children Hospital and collects cord blood routinely at these enrolled hospitals. To ensure that the cord blood is processed and infused to infants within 24 h after birth, the distance between these centers should be short. Furthermore, to reduce the differences in therapeutic treatment between the selected centers, a uniform guideline regarding the treatment of patients has been devised in all clinical centers. These centers hold quality control meetings every 3 months to ensure research consistency and report and analyze the possible side effects caused by MNC infusion. In this study, a total of 60 pairs of monozygotic twin premature infants fulfilling the eligibility criteria will be enrolled. For each pair, one random number will be assigned to the first baby of the twins; if the last digit of this random number is odd, the first baby will be assigned to the intervention group, and the second baby will be automatically assigned to the control group; in contrast, if the last digit of this random number is even, the first baby will be assigned to the control group, and the second will be automatically assigned to the intervention group. The protocol for this study has been developed based on the Standard Protocol Items: Recommendations for Interventional Trials (SPIRIT) checklist (Supplementary material S1, S2). We have followed the Consolidated Standards of Reporting Trials (CONSORT) guidelines and the study design is illustrated in Figure 1.

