### Blinding

The study data will be reviewed by the hospital ethics committee during the trial. Nobody will be made aware of the treatment-group assignments of the infants. After the enrollment is confirmed, the research assistants of the respective project leaders will confirm the random number. There will be at least one research nurse and physician in each center. Research nurses and physicians who are aware of the allocation of treatment will not be included in the babies’ care team and they will not participate in making care decisions for the babies in the trial. They will be asked to prepare the processed cord blood MNC or normal saline. Infusion bags will be covered with shading bags and MNCs will be infused by using a light-blocking infusion tube after preparation, so that the nurses who carry out the infusion and all physicians who treat the baby are not aware of the treatment assignment (Figures 2B,C). The infusion is then done by the supervisor nurse of the patients. The staff who collect and analyze the patients’ data and who follow up the patients are also blinded with the assignment. What is more, the infants’ parents are also not aware of the assignment. Therefore, this study is a double-blinded one.

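### The project principal sits on the board that decides on stopping from sequential analysis of the primary outcome, and this is not reconciled with the masking described under Blinding

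*Protocol article*

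**What the plan says.** Protocol article, Safety monitoring and co-intervention: the trial is overseen by a "safety monitoring board comprising an ethics committee member, project principal, good clinical practice member, and statisticians". After interim analyses held every 3 months, the board is to "make a decision on whether to stop or continue the trial based on safety monitoring and sequential analysis of the primary outcome". The section uses two slightly different names for the board; I read them as one body.

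Protocol article, Blinding: the section opens with the statement "Nobody will be made aware of the treatment-group assignments of the infants". It then describes "Research nurses and physicians who are aware of the allocation of treatment", who prepare the infusion and are kept out of care. It adds that "the research assistants of the respective project leaders will confirm the random number". The staff who gather and analyse the data, and those "who follow up the patients are also blinded with the assignment", are described as masked.

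The article does not say in what form the board receives the interim results. No sentence takes the project principal out of the review or the decision.

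**The concern.** People who run a trial are normally kept away from accumulating comparative results, because knowing the trend can change how they run it. They may recruit harder or more slowly, press for or against changes in conduct, or lean towards stopping or continuing for reasons other than the pre-set rule. Here the article fixes the membership of the board itself, and places the trial's leader on it. The board's remit goes beyond safety to the primary efficacy outcome. Followed as written, the principal has a part in every stop-or-continue decision made on that outcome, while the Blinding section presents the trial as one in which allocation is known to nobody.

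**Working it through.** No calculation settles this point, so the sections are set side by side. One short illustration is used at step 2.

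1. **Membership and remit.** Both are stated in Safety monitoring and co-intervention. The project principal is a named member, and the decision rests partly on sequential analysis of the primary outcome. Neither fact is inferred.

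2. **What a sequential analysis needs.** It monitors the difference between the arms. Pooled data cannot supply that.
   - Each pair puts one twin in each arm, so the arms are equal in size and the pooled rate is (pA + pB)/2.
   - The Sample size section gives pA = 0.30 and a 20% decrease. I read the decrease as absolute, so pB = 0.10. The section's own formula supports this at a two-sided 5% level: (0.30 × 0.70 + 0.10 × 0.90) × ((1.960 + 0.8416)/0.20)² = 0.30 × 196.2 = 58.9, or 59 per group against the stated 60.
   - With the planned effect, the pooled rate is (0.30 + 0.10)/2 = 0.20. With no effect and both arms at 0.20, it is (0.20 + 0.20)/2 = 0.20.
   - The pooled figure is the same in both cases. The board must therefore work from results split by arm, coded or not.

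3. **What the Blinding section allows.** It speaks of the assignments of infants. It names one group that knows them, the research nurses and physicians who prepare the product, and separates that group from care. It has no matching provision for a board member who leads the trial, and does not mention the board's by-arm results.

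4. **Consistency within the Blinding section.** The opening sentence says that nobody knows. A later sentence in the same section names staff who do. This is the only literal conflict, and it does not depend on the board.

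5. **Which routes to bias are closed.** Under Blinding, the physicians who treat the infants are masked. Safety monitoring and co-intervention applies uniform guidelines to ventilation, oxygen targets and postnatal steroids. Under Outcome measures, BPD status is judged by three independent experts who do not know the group. These protect bedside care and outcome classification.

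6. **Which routes stay open.** Enrolment, the general conduct of the trial by its leadership, and the stopping decision itself. None of the safeguards at step 5 reaches these.

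**The case against.** The strongest reply is that the two sections can both be true. Blinding concerns individual allocations, and a board can work from aggregate results with arms labelled A and B. The article never says that the principal learns any infant's arm. This stands, and it is why the point is one of non-reconciliation. It does not remove the point: coded arms still show the principal the size of the interim difference, and the article does not say that arms are coded.

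A second reply is that open and closed sessions belong in a board charter, and that a journal article may leave them there. That is fair for the mechanics. Membership, however, is stated in the article, and the statement includes the principal.

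Three stronger readings are tempting but not supported.

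- A reader might infer that the quarterly centre meetings, which "report and analyze the possible side effects caused by MNC infusion", also break the masking. The text says possible side effects. Suspected reactions to a masked infusion can be reviewed on timing and clinical picture, and nothing there says that allocations are disclosed.
- A reader might infer that interim knowledge would steer discretionary treatment such as postnatal steroids. That discretion belongs to the attending physician, the treating physicians are masked, and uniform guidelines apply. No sentence says that the principal treats trial infants.
- A reader might infer that by-arm counts would unmask an infant and, through the paired allocation, the co-twin. That needs very few events and a report that lets them be matched to infants; the article describes no such report.

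**Conclusion.** The point holds in this form: the trial's leader is placed on the body that takes efficacy-based stopping decisions, those decisions need a comparison by arm, and the article does not say how this fits with the masking under Blinding. It would be wrong to say that Safety monitoring and co-intervention flatly contradicts Blinding. The flat contradiction is inside the Blinding section, between its opening sentence and the staff it later describes as knowing the allocation.

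The size of the bias cannot be estimated from the document. Counting the planned looks would not measure it, since the number depends on the recruitment period and the primary outcome matures only at 36 weeks of postmenstrual age.

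The conclusion assumes that the two names for the board mean one body, and that no unseen charter already excludes the principal from by-arm review. If a charter does so, the article's wording still needs to match it. The change should be made; it is a cheap protection of trial integrity, and not evidence that bias has occurred.

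**What to change.** 1. In Safety monitoring and co-intervention, state that the project principal takes no part in the review of by-arm interim data or in decisions based on them, and attends only an open session with data pooled over arms.
2. In the same section, state that by-arm results go only to board members who are not involved in running the trial.
3. In Blinding, replace the opening claim that nobody knows the assignments with a list of who is unmasked: the research nurses and physicians who prepare the infusion, and any board members who see by-arm results. State whether the research assistants who confirm the random number are on that list.

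The cost is wording in two sections and in any board charter. The principal gives up access to comparative interim data. The article does not say whether a statistician on the board is independent of the running of the trial, or whether another member has clinical expertise. If either is lacking, a suitable member would have to be named.

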### Sample size

Our previous study showed that ACBMNC infusion was effective in reducing respiratory support duration in preterm infants (18). A randomized study in Korea by Won Soon Park showed that severe BPD incidence significantly reduced from 53% to 19% with mesenchymal stem cell intervention in the 23–24 GW group (*n* = 33) (20). The rate of BPD among very preterm infants at our NICU was 30% (pA), which is similar to the incidence rate reported previously (26). The sample size of this study was determined for assessing the efficacy of ACBMNCs compared with placebo with respect to the primary outcome in order to decrease the incidence of BPD or death with a two-sided α level of 0.05% and 80% power. We expect the intended (or at least acceptable) effect of ACBMNC infusion to be at a rate of 20% decrease in the frequency of BPD. To achieve this rate, at least 60 patients per group will be required based on the following formula:n=(pA(1−pA)/κ+pB(1−pB))((z1−α/2+z1−β)/(pA−pB))2)

κ = nA/nB is the matching ratio; α is type I error; β is type II error, meaning 1 − β is power.

Around 20 pairs of monozygotic twin births of less than 32 gestational weeks occur annually in Guangdong Women and Children Hospital and Dongguan Maternal and Child Health Hospital. Around 6 pairs of monozygotic twin births of less than 32 gestational weeks take place annually in Zhongshan Boai Hospital, Shunde Hospital, Southern Medical University, Dongguan Hospital, Southern Medical University, Nanfang Hospital, Southern Medical University, and Affiliated Maternal and Child Hospital of Foshan, Southern Medical University. Therefore, we assume that 60 pairs of monozygotic twins will be enrolled annually and the trial could be completed within 1 year.

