### Statistical analysis

Mean and standard deviation are reported for continuous variables, and the number and percentage are reported for categorical variables. Group comparisons of categorical variables for outcomes and co-interventions including death, BPD, and BPD severity are performed using nonparametric tests, the Fisher's exact test, or chi-square test, as appropriate. The relative risk (RR) is calculated as the ratio of the cumulative incidence rates of an event occurring in the intervention infusion group to the control group, and the number needed for treatment as the inverse of these two cumulative incidence rates. The results are shown as RR with 95% confidence interval (CI). For continuous variables, the mean values at each time point in each group of the variables are derived from a generalized linear model and the differences in the values over time are compared using an unpaired Student's t-test between the two groups. Kaplan–Meier cumulative incidence plots are generated to show time-to-event end points, namely, extubation and weaning to room air. All statistical tests are two-tailed, and *p*-values < 0.05 are deemed statistically significant. The Breslow–Day test and Cochran–Mantel–Haenszel (CMH) test will be used to adjust the data derived from different participating centers. The results will be reported as odds ratio (OR) with 95% CI. All statistical tests will be two-tailed and a *p*-value < 0.05 will be considered statistically significant. All statistical analysis will be performed using SPSS 21.0 (IBM).

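### Quarterly stopping decisions on the primary outcome are not reconciled with a blanket p < 0.05 and a single-look sample size, so the 5% error rate is not protected

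*Protocol article*

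**What the plan says.** Three parts of the protocol article bear on this.

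- Safety monitoring and co-intervention: "After each interim analysis (every 3 months), the data safety monitoring board will make a decision", and that decision is one to "make a decision on whether to stop or continue the trial based on safety monitoring and sequential analysis of the primary outcome". No boundary, spending function or number of looks is given.
- Statistical analysis: "All statistical tests will be two-tailed and a *p*-value < 0.05 will be considered statistically significant". The same threshold also appears earlier in that section. Neither statement makes an exception for interim looks or for a final test that follows them.
- Sample size: a fixed-sample formula for two proportions with 60 infants per group, stated for a "two-sided α level of 0.05% and 80% power". The timetable is that "we assume that 60 pairs of monozygotic twins will be enrolled annually and the trial could be completed within 1 year".

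The abstract places the primary outcome, survival without BPD, at 36 weeks of postmenstrual age.

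**The concern.** The quarterly reviews are not described as safety-only, since the primary outcome is one of the two stated grounds for stopping. Each look at that outcome that can end the trial is another chance to reject a true null hypothesis. Holding the overall rate at 5% requires stricter interim thresholds and, for most boundaries, a final threshold somewhat below 0.05. The only threshold the article states is 0.05, for every test.

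Two things are at stake. A positive primary result might not carry the error rate claimed for it. And an early stop at an unadjusted threshold would tend to exaggerate the effect, because only large observed differences cross when few pairs have been observed.

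**Working it through.** **1. The plan's own sample size.** Inputs from Sample size: pA = 0.30, 80% power, two-sided alpha, 1:1 ratio. The effect is worded "at a rate of 20% decrease in the frequency of BPD"; reading it as 20 percentage points gives pB = 0.10. Alpha is printed as 0.05%, but only 5% reproduces the stated figure.

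n = [0.30 × 0.70 + 0.10 × 0.90] × [(1.960 + 0.842) / 0.20]² = 0.30 × 196.2 = 58.9 per group.

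This agrees with the stated 60. It is a single-look calculation, and rounding 58.9 up to 60 leaves no allowance for interim looks. (Alpha of 0.05% as printed would give 141; a 20% relative reduction, pB = 0.24, would give 856. Both are separate points.)

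**2. Number of looks.** Quarterly looks over 1 year fall at months 3, 6, 9 and 12, so 4. Infants born before 32 weeks reach the 36-week assessment more than 4 weeks after birth, so outcomes maturing after month 12 could add a fifth. Eight looks would correspond to 2 years.

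**3. Overall two-sided error if |Z| > 1.96 is used at every one of K equally spaced looks.** Computed by recursive numerical integration for a correctly sized test:

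| K | 1 | 2 | 3 | 4 | 5 | 8 | 9 |
|---|---|---|---|---|---|---|---|
| Overall error | 5.0% | 8.3% | 10.7% | 12.6% | 14.2% | 17.6% | 18.5% |

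**4. If stricter interim bounds exist and only the final test stays at 0.05 (4, 5 or 8 looks).** With p < 0.001 at each interim look, overall error is 5.1-5.2%. With O'Brien-Fleming interim bounds it is 5.6-5.9%.

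**5. The tests the plan actually names.** Statistical analysis lists chi-square and Fisher tests, which ignore the twin pairing. Simulation of 60 pairs, null event rate 0.30, 40,000 runs per cell, p < 0.05 at every look; the within-pair correlations are assumed:

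| Test | Looks | Corr. 0 | Corr. 0.3 | Corr. 0.5 |
|---|---|---|---|---|
| Chi-square | 4-5 | 13.5-15.1% | 5.7-6.6% | 2.0-2.5% |
| Fisher | 4-5 | 7.0-7.6% | 2.3-2.7% | 0.6-0.8% |
| Chi-square | 8 | 17.6% | 8.1% | 2.6% |
| Fisher | 8 | 8.9% | 3.1% | 0.8% |

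A paired McNemar test gives 11.2-14.5% with 4-5 looks and 14.0-16.8% with 8, over the same correlations.

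**6. Exaggeration on early stopping.** With even accrual and no outcome lag, the first of 4 looks has 60/4 = 15 pairs. At a pooled rate of (0.30 + 0.10)/2 = 0.20, an unpaired test crosses 1.96 only if the observed difference exceeds 1.96 × √(2 × 0.20 × 0.80 / 15) = 0.286. That is about 29 percentage points, against 20 planned.

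**7. Thresholds that hold 5%.** Classical O'Brien-Fleming, equal looks: final |Z| of 2.024 (p = 0.043) for 4 looks, 2.040 (p = 0.041) for 5 and 2.072 (p = 0.038) for 8. A Pocock boundary would need p = 0.018, 0.016 and 0.012 at every look. Power cost under the plan's formula: the expected Z is 0.20/√(0.30/60) = 2.828. Final-look power is then Φ(2.828 − 1.960) = 80.7% at 0.05, Φ(2.828 − 2.024) = 78.9% with 4 looks and Φ(2.828 − 2.040) = 78.5% with 5. The loss is at most about 2 points, since interim crossings add back a little.

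**The case against.** A reader might infer that the trial's false-positive rate simply is 13-18%. The article does not support that, for four reasons.

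- It never says that 0.05 is the board's stopping criterion. Sequential analysis normally means a method that allows for repeated looks, and a boundary may well sit in a charter or SAP that is not shown. Its absence from a journal article is not in itself a fault.
- The sentence stands under a safety heading and says stop or continue, not stop for benefit. Stopping only for futility or harm does not raise the chance of falsely claiming benefit.
- The named tests ignore the pairing. With positive within-twin correlation they are conservative, and the realised rate could be near or below 5%.
- The 18% figure needs about 8 looks, whereas the plan is 1 year.

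All four limit the number; none removes the conflict. The article is not silent on the threshold: it prints 0.05 for all tests, so an unseen boundary that lowers the final level would still contradict it. Nothing restricts use of the primary outcome to futility or harm. The conservatism of the unpaired tests depends on an unknown correlation and comes from discarding the pairing that the Discussion relies on for power. With a paired test the inflation returns almost in full.

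A reader might also infer that recruitment must overrun and so add looks. The birth counts are ambiguous. Read per hospital, 2 × 20 + 5 × 6 = 70 pairs a year exceeds 60. Read as two totals, 20 + 6 = 26 a year means 60/26 = 2.3 years and about 9 looks. An overrun is possible but not established, and the point does not need it. What matters is that calendar-based looks have no stated cap.

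**Conclusion.** The point stands as an unreconciled rule: stopping every 3 months on the primary outcome, a blanket two-sided 0.05 and a single-look sample size cannot all be followed while holding overall error at 5%.

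Its size depends on what the board does. If 0.05 were used at each look with a correctly sized test, overall error would be about 13-14% on the 1-year plan and about 18% if slow accrual led to 8 looks. If strict interim bounds exist and only the final test stays at 0.05, it would be about 5.1-5.9%. These figures assume equally spaced looks and, for the upper range, that any crossing stops the trial and is reported as significant. The realised rate with unpaired tests may be lower; the documents give no within-pair correlation from which to say by how much. The article therefore supports the statement that 5% is not protected. It does not support any single figure as the trial's actual error rate.

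**What to change.** Choose one of the following before any interim comparison of the primary outcome, and word Safety monitoring and Statistical analysis to match.

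(a) State that the quarterly reviews are for safety only, with no stopping for benefit, and keep one final primary test at 0.05. This needs no change to the sample size or threshold. The cost is giving up the option to stop early for benefit.

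(b) Specify an O'Brien-Fleming-type Lan-DeMets spending function, with information measured by the number of pairs that have a 36-week outcome, and schedule efficacy looks by that count rather than by calendar quarter. For the primary outcome, replace the blanket 0.05 with the resulting final level. The classical values of about 0.043 for 4 equally spaced looks and 0.041 for 5 are a close guide; the exact level should be computed for the chosen timing. The boundary should be computed for the primary test that will actually be used. The cost is a slightly stricter final threshold, about 2 points of power at most under the plan's own assumptions.

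If a boundary already exists in the charter or SAP, cite it in the protocol and correct the 0.05 statement accordingly.
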